#### Other assessments

Other assessment tools include the Charlson Comorbidity Index [26]; the Instrumental Activities of Daily Living [13], the Geriatric Depression Scale [27], and the Short Form Health Survey [28], and will be assessed at baseline, at 3 months, and 1 year postoperatively. Subjective grading of cognitive functions and subjective grading of pain are determined on numeric rating scales at baseline, 7 days, 3 months and 1 year postoperatively. Subjective grading of change in cognitive functions (five-point Likert scale) and subjective grading of successful surgery (yes/no) are assessed at 7 days, 3 months and 1 year postoperatively.

#### Magnetic resonance imaging

Cerebral MRI will be performed at baseline, at 3 months, and 1 year postoperatively on the same day as the neuropsychological assessment. MRI analysis will be carried out by the Division of Neuroradiology at the University Hospital Basel. High-resolution anatomic and diffusion cerebral MRI will be performed using the hospital’s 3-Tesla MAGNETOM Prisma™ MRI scanner (Siemens, Zurich, Switzerland). For MRI analysis, we will assume that the same regions as those described in mild cognitive impairment and Alzheimer’s disease [29] are relevant to POCD. We will perform a region of interest (ROI) analysis (hippocampus, lateral ventricle, total grey matter volume, regional cortical thickness). Cortical reconstruction and volumetric segmentation will be performed with the FreeSurfer software suite [30], which is freely available for download online (http://surfer.nmr.mgh.harvard.edu).

### Statistics

#### Sample size justification

Sample size is estimated based on data describing hippocampal volume. The clinically relevant difference is defined as the difference in hippocampal volume between normal subjects (2.8 ± 0.5 cm^3^) and patients with mild cognitive impairment (2.4 ± 0.4 cm^3^) [29]. Assuming an incidence of POCD of 41% one week after surgery in this age group [2], and a standard deviation of the hippocampal volume change of 0.45 in both patients with and without POCD, a total sample size of 56 subjects may detect a difference of 0.4 cm^3^ in hippocampal volume [29] with a power of 90% at a two-sided significance level of 5%. To compensate for the high loss to follow-up, which is unfortunately typical for studies on POCD [31] and estimated at 20%, we will recruit 70 patients in the surgical group (Group 1). The number of study participants in the nonsurgical control group (Group 2) is arbitrarily set at 30.

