## Background

Anesthesia care for patients in their seventies or eighties has an ever-growing presence in clinical practice given the demographic development in many industrialized countries. Variable degrees of cognitive decline are frequently observed after major surgery in elderly patients and have been defined as postoperative cognitive dysfunction (POCD) [1]. Clinical studies have reported an incidence of POCD of up to 41% in surgical patients older than 60 years (Table 1) [2]. In many patients, this is a transient problem. But in some patients, cognitive deficits are long-term or permanent [1, 2]. POCD may also develop in younger patients [3] and after minor surgery [4]. The occurrence of POCD is associated with increased mortality and important socioeconomic consequences [5].

**Table 1 Tab1:** Incidence of POCD after noncardiac surgery

Study	Population	Time for postoperative test	POCD rate (%)
Moller et al. [1]	Patients ≥60 undergoing major abdominal, thoracic, or orthopedic surgery	1 week and 3 months	25.8 and 9.9%, respectively
Monk et al. [2]	Patients >60 undergoing minimally invasive, intraabdominal/thoracic, or orthopedic surgery	1 week and 3 months	41.4 and 12.7%, respectively
Johnson et al. [3]	Patients 40–60 undergoing major abdominal or orthopedic surgery	1 week and 3 months	19.2 and 6.2%, respectively
Canet et al. [4]	Patients >60 undergoing minor surgery	1 week and 3 months	6.8 and 6.6%, respectively

*POCD* postoperative cognitive dysfunction

The potential association between exposure to anesthesia and the development of dementia in elderly patients remains a controversial topic [6, 7]. So far, a direct association between surgery and long-term cognitive decline has not been established [8]. The pathophysiology of POCD is poorly understood, and no preventive strategy or treatment has been described so far [9]. A retrospective analysis of cohort data suggests that surgery may be associated with a decrease in brain volume [10]; however, no analysis of a potential link between cerebral atrophy and cognitive functions was made. We would like to reproduce and verify these results and investigate a possible relationship with the postoperative cognitive performance in surgical patients.

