### Outcomes

The primary endpoint of this study is the degree of change in hippocampal volume over time between patients with and patients without POCD. Other specific cerebral volumes measured are the lateral ventricles, the total grey matter volume, and regional cortical thickness. The secondary endpoint is the correlation between the change in cerebral volume and the change in cognitive function.

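### The 90% power rests on the one-week POCD incidence of 41%, but hippocampal change is measured at 3 months and 1 year and no POCD visit is named; if 3-month POCD at Table 1 rates defines the groups, power is about 50-58%

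*Protocol article*

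**What the plan says.** **Endpoint (Protocol article, Outcomes).** "The primary endpoint of this study is the degree of change in hippocampal volume over time between patients with and patients without POCD". No visit is attached to POCD status, and no interval to the volume change.

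**Power (Sample size justification).** The inputs are "Assuming an incidence of POCD of 41% one week after surgery in this age group [2"], "a standard deviation of the hippocampal volume change of 0.45 in both patients with and without POCD", and "a total sample size of 56 subjects" that "may detect a difference of 0.4 cm^3^ in hippocampal volume" "with a power of 90% at a two-sided significance level of 5" per cent. Allowing for 20% loss, 70 surgical patients are recruited.

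**Imaging (Magnetic resonance imaging).** "Cerebral MRI will be performed at baseline, at 3 months, and 1 year postoperatively on the same day as the neuropsychological assessment". There is no one-week scan.

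**Cognition (Neuropsychological assessment).** The battery is given before surgery, at 7 days, at 3 months and at 1 year, so POCD can be diagnosed at three visits.

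**Abstract, Methods.** Brain volumes and cognition are compared before surgery and at 3 and 12 months. The 7-day visit is not part of that comparison.

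**Expected incidence (Background, Table 1).** For the study that supplies the 41%, the rates at 1 week and 3 months are "41.4 and 12.7%, respectively". The other study of major surgery in patients aged 60 or over reports 25.8% and 9.9%. No 12-month rate is given.

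**The concern.** For a fixed total, the power of a two-group comparison depends on how evenly the total splits. A 41/59 split is close to balanced. A split near 10/90 is not, and the small group then dominates the standard error.

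The protocol takes its split from the first week after surgery, while the outcome exists only from 3 months on. Its own table shows that POCD is far rarer by then, and the Background says that the problem is transient in many patients. The 90% therefore holds for a grouping by early POCD that the endpoint does not state.

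At stake is how the sole primary comparison is read. If the groups turn out to be about 6-7 patients against about 50, a null result could be taken as evidence of no association when the comparison had roughly an even chance of detecting the difference it was designed for.

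**Working it through.** **Inputs.** Difference d = 0.4 cm³, SD of change s = 0.45 in both groups, two-sided α = 0.05 and N = 56 evaluable, all from the Sample size justification. Incidence p is 0.41 (same paragraph), or 0.127 and 0.099 (3-month column of Table 1).

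**Formula.** n₁ = N·p and n₂ = N − n₁. SE = s·√(1/n₁ + 1/n₂), and the noncentrality is d/SE. Power is the probability that a noncentral t with 54 degrees of freedom exceeds 2.005; the opposite tail is negligible.

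**Step 1: reproduce the plan.** At p = 0.41, n₁ = 56 × 0.41 = 23.0 and n₂ = 33.0.
- SE = 0.45·√(1/23 + 1/33) = 0.122 and noncentrality = 0.4/0.122 = 3.27.
- Power is 89.5% by t, or 90.5% by the normal approximation.
- N for 90% power is 55 (normal) or 57 (t), against 56 stated. Recruitment is 56/0.8 = 70.

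The stated figures are correct for their inputs.

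**Step 2: change only the incidence, to the 3-month rates.**
- p = 0.127: n₁ = 7.1, n₂ = 48.9, SE = 0.181, noncentrality = 2.21, power 58.5%. With whole patients, 7 versus 49, it is 58.0%.
- p = 0.099: n₁ = 5.5, n₂ = 50.5, SE = 0.201, noncentrality = 1.99, power 49.7%. With 6 versus 50 it is 52.4%.
- The normal approximation gives 60.1% and 51.1%.
- Averaged over the random number of cases, power is 56.5% and 47.8% (t).

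**Step 3: difference detectable with 90% power at N = 56 (t).** 0.40 cm³ at 41%, 0.60 cm³ at 12.7% and 0.66 cm³ at 9.9%.

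**Step 4: range of incidence.** The incidence under this study's own rule is unknown, so the 20% and 30% rows are assumptions.

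| POCD incidence | Expected cases of 56 | Power for 0.4 cm³ (t) |
|---|---|---|
| 10% | 5.6 | 50% |
| 13% | 7.3 | 59% |
| 20% | 11.2 | 74% |
| 30% | 16.8 | 85% |
| 41% | 23.0 | 89.5% |

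**The case against.** The strongest reply is that nothing has been miscalculated and that the plan may mean what the sample size paragraph says. POCD is tested at 7 days, and that paragraph ties the incidence to one week. Comparing later hippocampal change between patients with and without early POCD is a coherent cohort contrast, and under it about 90% power stands. This part of the reply holds, and it is why the lower figures are conditional. It does not settle the matter, because the endpoint never says that 7-day status defines the groups and the abstract points to 3 and 12 months.

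A second reply also holds. The Table 1 rates come from other studies, and the section on diagnosis of POCD says that criteria differ widely. Here POCD is a decline of more than 1.0 standard score in at least two of 15 variables, which could yield an incidence well above 10-13%. The 41% is borrowed in the same way, so the argument supports showing a range rather than keeping one favourable value.

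Three stronger readings are tempting, and the documents do not support them:
- **The same-day rule fixes the grouping.** A reader might infer that pairing imaging with cognition tested on the MRI day makes 3-month POCD the grouping. In the Statistical analysis plan section that sentence concerns correlation with the CERAD-NAB total score, not the POCD split.
- **The low rates apply at 12 months too.** Table 1 stops at 3 months.
- **Several possible visit pairings inflate type I error.** No text proposes choosing among them after seeing the data. They share patients and baseline scans, so a figure that assumes independent tests would not apply.

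A condensed article may leave the primary visit to a fuller document. The point here is narrower: a stated power input does not match the stated imaging schedule or the article's own table.

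**Conclusion.** The point holds in conditional form. The 90% power is tied to a POCD visit at which no MRI is done, and the endpoint does not name that visit as the one that forms the groups.

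- **Groups by 3-month POCD at Table 1 rates (9.9-12.7%):** about 6-7 cases among 56, power about 50-58% for 0.4 cm³, and 90% power only for about 0.60-0.66 cm³.
- **Groups by 7-day POCD at 41%:** about 90% stands.
- **Groups by 12-month POCD:** the documents give no incidence, so no power can be stated.

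These figures keep the protocol's difference, SD, 56 evaluable patients and equal variances. A reader might conclude that the study's actual power is 50-58%. That goes too far, because it presupposes both a grouping that the protocol leaves open and an incidence from studies with other criteria. The abstract makes the 3-month or 12-month grouping the better-supported reading, but it is not stated.

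**What to change.** 1. In Outcomes, name one primary contrast: the visit whose POCD status defines the groups, and the MRI interval over which hippocampal change is taken.
2. In the Sample size justification, restate power for the incidence expected at that visit. Show it over a range such as 10%, 13%, 20%, 30% and 41%, and note that the rates come from studies with other POCD criteria.
3. If 7-day POCD is meant, say so in the endpoint and in the conclusions, and give the 3-month power beside it.

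Leave N at 70 recruited and 56 evaluable. The cost is rewording two paragraphs, with no extra patients, visits or scans. The downside is that the stated power may become less favourable than 90%.

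### The 90% power claim uses a cross-sectional volume gap, and an SD with no longitudinal source, for an endpoint that is a difference in change

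*Protocol article*

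**What the plan says.** Under Outcomes, the Protocol article makes the primary endpoint "the degree of change in hippocampal volume over time between patients with and patients without POCD". Under Magnetic resonance imaging, scans are at baseline, 3 months and 1 year, so change is measured over at most a year.

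Under Sample size justification, the target comes from a different kind of quantity: "The clinically relevant difference is defined as the difference in hippocampal volume between normal subjects" on one side and a mildly impaired group on the other. The impaired group's volume is given as 2.4 ± 0.4 cm³, the normal group's as 2.8 ± 0.5 cm³. The same paragraph assumes "a standard deviation of the hippocampal volume change of 0.45 in both patients with and without POCD" and concludes that 56 subjects "may detect a difference of 0.4 cm^3^ in hippocampal volume" at 90% power, two-sided 5%. The group split comes from a 41% incidence of POCD at one week. Adding 20% loss to follow-up gives 70 surgical patients. No longitudinal study is cited for the SD of change or for an expected difference in change.

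**The concern.** A power statement describes an endpoint only if its effect and its SD are on that endpoint's scale. Here the effect is a difference in level between two groups of different people, while the endpoint is a difference between groups in within-patient change. The SD is labelled as one of change, but its value coincides with the average of two between-person SDs of level. The SD of a within-person change can be much smaller or larger than the SD of level, depending on how strongly the two scans correlate.

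Two things are at stake. First, a reader cannot tell from the paragraph which difference in change the study can detect, so a null result would be hard to interpret. Second, the article sets its threshold of clinical relevance at 0.4 cm³. Carried over to change, that threshold would class a true extra loss of 0.1 or 0.2 cm³ within a year as not relevant, and nothing in the document argues for that.

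**Working it through.** **Inputs.** From Sample size justification: means 2.8 and 2.4 cm³, SDs 0.5 and 0.4, target 0.4 cm³, SD 0.45, POCD 41%, two-sided α 0.05, power 90%, 56 evaluable, 20% loss. Assumed, because the document does not give it: r, the correlation between a patient's baseline and follow-up hippocampal volume.

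**1. Reproduce the plan's figure.** Let k = 0.41/0.59 = 0.695 be the ratio of POCD to non-POCD patients.
- Non-POCD patients needed = (1 + 1/k) × [0.45 × (1.960 + 1.282)/0.4]² = 32.4; POCD patients = 0.695 × 32.4 = 22.5.
- Rounding up gives 33 + 23 = 56.
- Power at 23 v 33 is 90.5% by normal approximation and 89.5% by t-test.
- 56/0.8 = 70.

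The arithmetic is right for a standardised difference of 0.4/0.45 = 0.89.

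**2. Where the inputs come from.**
- Target: 2.8 − 2.4 = 0.4 cm³, a cross-sectional difference in level. The article says so itself.
- SD: (0.5 + 0.4)/2 = 0.45 exactly (root mean square 0.453). That this is the origin of the 0.45 is an inference.

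**3. What 0.4 cm³ means as a difference in change.** 0.4/2.8 = 14.3%. POCD patients would have to lose 14% of a 2.8 cm³ hippocampus beyond whatever non-POCD patients lose. That is the whole normal-to-impaired gap arising within at most a year, in a cohort from which dementia and a baseline MMSE below 24 are excluded.

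**4. What 0.45 means as an SD of change.** If the between-person SD is 0.45 at both scans, SD of change = 0.45 × √(2(1 − r)). This equals 0.45 only when r = 0.5.

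**5. Difference in change detectable with 90% power, 23 v 33.** For a two-sided t-test with 54 degrees of freedom, this is 0.897 × SD of change.

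| Assumed r | SD of change (cm³) | Detectable difference (cm³) | % of 2.8 cm³ |
|---|---|---|---|
| 0.50 | 0.45 | 0.40 | 14 |
| 0.80 | 0.28 | 0.26 | 9 |
| 0.90 | 0.20 | 0.18 | 6 |
| 0.95 | 0.14 | 0.13 | 5 |
| 0.98 | 0.09 | 0.08 | 3 |

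**6. The two borrowed inputs can pull in opposite directions.** Power at 23 v 33 by t-test, for assumed differences in change:

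| Difference (cm³) | SD 0.45 | SD 0.20 | SD 0.10 |
|---|---|---|---|
| 0.20 | 36% | 95% | >99% |
| 0.10 | 13% | 44% | 95% |
| 0.05 | 7% | 15% | 44% |

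A true difference below 0.4 lowers power and an SD below 0.45 raises it. The document fixes neither, so the net effect is unknown.

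**The case against.** The article labels 0.45 as an SD of change, and no sentence says it was taken from the two cross-sectional SDs. The source cited for the volumes is not to hand. This stands as a limit on certainty: the origin of the 0.45 is a strong inference, not an established fact. The cross-sectional origin of the 0.4 is not in doubt, and the absence of a longitudinal source for the 0.45 is visible on the page.

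A reader might infer that the study is underpowered, since the same 23 v 33 at SD 0.45 gives only 13% power for 0.10 cm³. The document does not support that. Those figures pair a smaller difference with the very SD that is in question. At r = 0.8, power for 0.4 cm³ exceeds 99%. Nor does the document support the opposite claim that change is surely far less variable: r is unknown, and it is the correlation over months, including real differences in atrophy, not scan-rescan repeatability.

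The study describes itself as having pilot character, says only that 56 subjects may detect the difference, and explains the anchor on mild cognitive impairment as a deliberate assumption about which brain regions matter (Magnetic resonance imaging; Endpoints). That justifies the choice of regions. It does not turn a difference in level into a difference in change, and an explicit 90% claim should be correct even in a pilot. What does stand is that the correction alters no visit, group, endpoint or recruitment target.

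**Conclusion.** The sample-size paragraph is wrong as written. Its 90% applies to a cross-sectional contrast of d = 0.89 between normal and mildly impaired subjects, not to the difference in hippocampal change that is the primary endpoint. The arithmetic is sound, and N = 70 is not shown to be wrong in either direction.

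The size of the problem is the uncertainty it hides: over r from 0.5 to 0.98, the difference detectable with 90% power at 23 v 33 varies about fivefold, from 0.40 to 0.08 cm³. This rests on an assumed r, an equal between-person SD of 0.45 at both scans, and the article's 41% split. Whether a one-week incidence should set that split when MRI is at 3 and 12 months is a separate question and adds no weight here.

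**What to change.** Keep N = 70 and rewrite the paragraph:

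1. Withdraw the statement that 56 subjects give 90% power for 0.4 cm³.
2. Define the clinically relevant difference as a difference in change, POCD versus no POCD, over one named interval (3 or 12 months).
3. Restate the sample size as the difference in change detectable with 90% power, tabulated over assumed baseline-to-follow-up correlations from 0.5 to 0.98 as above, with the equal-SD assumption stated.
4. Once enough surgical participants have follow-up MRI, update the table with the observed SD of change, pooled and not split by POCD status, and report its confidence interval.

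The planned look at 20 participants should not be relied on for step 4. The article describes it as a check of data quality after primary data acquisition. It does not say that those participants will have follow-up scans or that all will be surgical patients. Even 20 complete pairs would give a 95% interval for the SD of about 0.76 to 1.46 times the estimate (chi-square, 19 degrees of freedom).

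The cost is one rewritten paragraph and, later, one pooled SD. No extra patients or scans are needed. The downside is that the paragraph loses its single headline power figure.

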#### Statistical analysis plan

The quantitative imaging results will be correlated to the CERAD-NAB total score performance obtained on the same day as the MRI scans. The relationship of changes in volume with intraoperative depth of anesthesia (BIS) and the administered dose of sevoflurane expressed as age-corrected minimum alveolar concentration (MAC) equivalent [32] multiplied by time of administration will be calculated. We will use voxel-wise, multivariate analysis of variance (ANOVA) and the classification/prediction procedure on multi-parameter MRI data in order to build optimal composite predictors of patients’ neuropsychological outcomes. All statistical analyses will be performed using SPSS Statistics software, version 22 (IBM, Inc., Zurich, Switzerland). All graphs will be plotted using Prism, version 6 (GraphPad Software, Inc., La Jolla, CA, USA). An interim analysis will be performed to assess quality of data after primary data acquisition from 20 participants. We will follow the Strengthening the Reporting of Observational studies in Epidemiology (STROBE) statement [33] for all future reports related to this study.

### Data monitoring and stopping rules

The EC agreed that monitoring would be performed by the interdisciplinary study team. This team will evaluate the progress of the trial, verify the accuracy and completeness of the case report forms, and ensure that all protocol requirements and investigator’s obligations are being fulfilled. The progress of the trial is evaluated every 6 months. The investigators may terminate the study prematurely according to certain circumstances (e.g., ethical concerns, insufficient participant recruitment, when the safety of the participants is doubtful or at risk, or when alterations in accepted clinical practice make the continuation of a clinical trial unwise).

### Study safety and reporting of adverse events

There are no specific safety concerns related to this study. During initial screening of participants in the recruitment phase, any subject that presents potential safety concerns related to MRI will be excluded from the study. Above all, MRI does not use ionizing radiation, and there are no known harmful side-effects associated with temporary exposure to the strong magnetic field used by MRI scanners [34]. However, if a serious adverse event should occur, it will be reported to the EC within the appropriate time frame.

## Discussion

This observational cohort study prospectively evaluates the relationship of cerebral grey matter volume and POCD in elderly patients after major noncardiac surgery under sevoflurane anesthesia. The primary hypothesis of this investigation is that POCD is accompanied by a loss of cerebral grey matter. Our secondary hypothesis is that the degree of POCD correlates with the loss of grey matter in brain areas relevant for cognitive functions. There are several potential implications of this study for future clinical practice. The validation of reproducible anatomical parameters or biomarkers, such as the specific brain volumes examined in our cohort, will help to identify high-risk patients and may serve to evaluate the effect of preventive strategies and treatment interventions for POCD in clinical follow-up studies. In summary, findings of this study may contribute to improve the diagnosis and prevention of POCD in the future. In the following, we discuss considerations regarding study design, endpoints, choice of study collective, surgical procedures and anesthetic technique.

